## 1. Introduction

Blood glucose (BG) variability in diabetic and non-diabetic patients is independently associated with increased morbidity and mortality in the intensive care unit and after cardiac events.^[1–3]^ In cardiac surgery patients, BG variability is reported to be associated with severe postoperative complications – leading to an increase length of intensive care unit (ICU) stay – regardless of the quality of BG control obtained during the perioperative period.^[4–6]^

Several hypotheses have been raised to explain the deleterious effect of BG variability observed in diabetic patients. Basal state BG variability seems to depend on the diabetes phenotype and to differ between people with or without diabetes.^[7,8]^ Furthermore, some studies suggest an association between BG variability and the activity of the autonomic nervous system (ANS).^[9–13]^ Finally, other studies highlight that the deleterious effect of BG variability includes increased oxidative stress, endothelial dysfunction, and cell apoptosis.^[14–16]^ However, no study has specifically addressed this issue in cardiac surgery patients and the underlying mechanisms contributing to increased perioperative BG variability and to its deleterious impact remain unclear.

The aim of this study is to investigate whether postoperative GV could be related to preoperative GV and/or to perioperative alteration of the ANS activity in diabetic and non-diabetic cardiac surgery patients and the relationship between postoperative GV and blood and urinary level of inflammation and endothelial dysfunction biomarkers.

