## 2. Objectives

The primary objective is to describe the relationship between baseline (preoperative) and postoperative BG variability within 48 hours after surgery.

Secondary objectives are: to describe the relationship between baseline and postoperative BG variability within 48 hours after surgery according to the diabetic status and to the type of surgery; to describe the relationship between the preoperative activity of the ANS and the baseline BG variability; to describe the relationship between the preoperative activity of the ANS and the postoperative BG variability within 48 hours after surgery; to describe the relationship between postoperative BG variability within 48 hours after surgery and the postoperative activity of the ANS within 48 hours after surgery; to describe the relationship between postoperative BG variability within 48 hours after surgery and the diabetes phenotype; to describe the relationship between postoperative BG variability within 48 hours after surgery and the urinary and blood level of biomarkers of inflammation and of endothelial dysfunction; and to describe the morbidity and the mortality within 30 days after surgery.

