### 3.2. Eligibility

Adult patients who undergo planned on-pump coronary artery bypass surgery or aortic valve replacement surgery in the University Hospital of Besancon, France (Centre Hospitalier Universitaire (CHU) de Besancon) will be eligible for inclusion.

Four groups of 30 patients will be studied: group 1, including insulin-requiring type 2 diabetic patients undergoing on-pump coronary artery bypass graft (CABG); group 2, including non-insulin-requiring type 2 diabetic patients undergoing on-pump CABG; group 3, including non-diabetic patients undergoing aortic surgical valve replacement; and group 4, including non-diabetic patient undergoing on-pump CABG.

Inclusion and exclusion criteria for the present study are listed below.

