### 3.8. Outcome measures

The primary outcome will be the mean difference between the preoperative (baseline) and the postoperative CV, and its 95% confidence interval, measured using the subcutaneous glucose sensor Abbott® Free Style Libre Pro.

Secondary outcomes will: the preoperative and postoperative BG variability, quantified by the preoperative and postoperative values of: the SD of BG, the CV, the MAGE, the glycemic lability index and the glycemic penalty index; the preoperative and postoperative activity of the ANS, quantified by the preoperative and postoperative values of: the COMPASS 31 score, the LF, the HF, the LF/HF ratio, the RMSSD, the SDNN, the SDANN, and the pNN50; the diabetes phenotype, described by the preoperative fasting BG and glycosylated hemoglobin values; the blood and urinary levels of biomarkers of inflammation (IL^-^2, IL^-^6, IL^-^10, TNF^-^alpha, 8^-^iso^-^prostanglandin^-^F_2*α*_) and of endothelial function [Endocan, angiopoietin^-^1 (Ang^-^1), angiopoietin^-^2 (Ang^-^2), vascular endothelial (VE)^-^cadherin]; and postoperative morbidity and mortality at day 30 after surgery. Postoperative morbidity includes cardiac arrest, stroke, cardiac arrhythmia requiring therapeutic intervention, surgical wound infection, pneumonia, renal failure requiring dialysis, sepsis, surgical revision, readmission in the intensive care unit or in hospital.

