### 3.11. Sample size calculation

Four groups of patients will be included to describe the relationship between preoperative (baseline) and early postoperative BG variability in diabetic (groups 1 and 2) and non^-^diabetic patients (groups 3 and 4), and between BG variability and the ANS activity in patients treated (groups 1, 2 and 4) or not (group 3) with beta^-^blockers: group 1, including patients with insulin^-^requiring type 2 diabetes mellitus undergoing planned on^-^pump CABG surgery; group 2, including patients with non^-^insulin^-^requiring type 2 diabetes mellitus undergoing planned on^-^pump CABG surgery: group 3, including non^-^diabetic patients undergoing planned aortic valve replacement surgery; and group 4, including non^-^diabetic patients undergoing planned on^-^pump CABG surgery.

No previous study has described the difference between the preoperative (baseline) and the early postoperative CV (primary outcome) in cardiac surgery patients. Thus, no assumption can be made on the expected value of the primary outcome. The sample size calculation was based in the expected measurement accuracy of the primary outcome in each group.

Considering an alpha risk at 0.05 and an estimated standard deviation of CV of 8.2 (basal state) (RE Pratley, 2018 Nov), we hypothesized that the 95% confidence interval range of the difference between the baseline and the early postoperative CV will be no more than 6.12 (conservative assumption considering that the variance will be lower because of the repeated measurement of CV in the same patients). A sample size of 30 patients per group was calculated using the PASS software (“Confidence Intervals for 1 Mean” method, Hahn, G.J. and Meeker, W.Q. 1991. Statistical intervals. John Wiley & Sons. New York).

Thus, the inclusion of a total sample size of 120 patients (30 patients per group) is planned.

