### 3.12. Statistical analysis

Categorical variables will be compared using the Chi^-^square test or Fisher’s exact test. Normally distributed quantitative variables will be compared using the Student *t* test or an analysis of variance (ANOVA). Non^-^normally distributed quantitative variables will be analyzed using the non^-^parametric Wilcoxon or Kruskall^-^Wallis tests. Statistical tests for repeated measures will be used for before^-^ after comparisons (paired Student *t* test or paired Wilcoxon test, 1^-^way ANOVA with repeated measures or Friedman test).

The primary outcome will be described using the mean and the 95% confidence interval of the mean. The temporal trend of preoperative, intraoperative, and postoperative BG variability will be described by the mean and the 95% confidence interval of the mean of each variable describing BG variability and figured as boxplot. The relationship between preoperative and postoperative BG variability, between BG variability and the ANS activity and between the postoperative BG variability and the blood and urinary level of biomarkers of inflammation and endothelial function will be investigated using the Pearson or the Spearman correlation coefficient and univariate linear regression models and presented on adequate figures.

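### The baseline-to-postoperative glucose variability relationship is analysed by correlation and one-predictor regression across four quota groups; without a group term the coefficient can mix between-group gaps with the within-group relationship

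*Protocol article*

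**What the plan says.** Section 2 of the protocol states: "The primary objective is to describe the relationship between baseline (preoperative) and postoperative BG variability within 48 hours after surgery". A separate secondary objective covers the same relationship "according to the diabetic status and to the type of surgery".

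Section 3.12 gives the method. The relationships between preoperative and postoperative variability, between variability and autonomic (ANS) activity, and between postoperative variability and biomarkers "will be investigated using the Pearson or the Spearman correlation coefficient and univariate linear regression models". The section names no adjusted, stratified or interaction analysis and does not say whether the coefficients are computed over all patients or by group.

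The sample is built by quota. Section 3.2: "Four groups of 30 patients will be studied". Section 3.11: "the inclusion of a total sample size of 120 patients (30 patients per group) is planned". The groups are defined by diabetes status, insulin requirement and type of surgery. Section 1 gives a reason to expect them to differ before surgery: "Basal state BG variability seems to depend on the diabetes phenotype and to differ between people with or without diabetes".

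The named primary outcome is a different quantity. Section 3.8: "The primary outcome will be the mean difference between the preoperative (baseline) and the postoperative CV", with its 95% confidence interval.

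**The concern.** The primary and secondary objectives differ only in whether the relationship is broken down by diabetic status and surgery. Unless they duplicate each other, the primary one is taken over all 120 patients. A univariate regression has one predictor, so a pooled version has no place for group.

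The introduction asks whether postoperative variability could be related to preoperative variability. Suppose the diabetic groups are higher at both times, but inside each group a patient's baseline value says nothing about the postoperative value. The pooled coefficient is then still positive. It cannot separate that situation from one in which a patient's own baseline carries information beyond group membership. Its size also reflects the equal quotas, which are a design choice and not a feature of any patient population.

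At stake is the interpretation of the analysis that most directly answers the primary objective as worded, since a mean difference does not by itself describe how baseline and postoperative values are related.

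**Working it through.** **The plan's own figure.** Section 3.11 uses an SD of CV of 8.2, a 95% interval and a full width of 6.12. Width = 2 × t(0.975, 29) × SD/√n = 2 × 2.045 × 8.2/√30 = 6.124. The stated 30 per group reproduces. The same SD of 8.2 is used below for both time points.

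**Inputs.** From the protocol: four groups of 30, SD 8.2, alpha 0.05. Assumed: the group means before and after surgery, because the protocol gives none, and a true correlation of zero inside every group.

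**Formula.** With zero within-group covariance and equal group sizes,

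pooled r = C / √[(V₁ + s²)(V₂ + s²)],

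where V₁ and V₂ are the variances of the four group means before and after surgery (divisor 4), C is their covariance, and s² = 8.2² = 67.24.

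**Scenarios (groups 1 to 4).**

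1. *Any baseline gap, no postoperative gap.* C = 0, so r = 0.
2. *Graded 1 SD baseline shift (8.2, 4.1, 0, 0), halved after surgery (4.1, 2.05, 0, 0).* V₁ = 11.56, V₂ = 2.89, C = 5.78. r = 5.78/√(78.80 × 70.13) = 0.08.
3. *Both diabetic groups 1 SD higher before (8.2) and 0.5 SD higher after (4.1).* V₁ = 16.81, V₂ = 4.20, C = 8.41. r = 8.41/√(84.05 × 71.44) = 0.11.
4. *Means 32/26/18/18 before and 22/19/16/16 after.* V₁ = 34.75, V₂ = 6.19, C = 14.63. r = 14.63/√(101.99 × 73.43) = 0.17.

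**Share of simulated trials of 120 patients with p < 0.05** (pooled test on 118 df; with the group factor, 115 df). Ranges span separate simulation runs.

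| Scenario | Pooled r | Pooled, p < 0.05 | With group factor |
|---|---|---|---|
| 1 | 0 | about 5% | about 5% |
| 2 | 0.08 | 13–14% | about 5% |
| 3 | 0.11 | 21–22% | about 5% |
| 4 | 0.17 | 45–47% | about 5% |

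The effect can be larger. With both diabetic groups a full 1 SD higher at both times, r = 16.81/84.05 = 0.20, significant in 60%. It can also vanish: with gaps of 0.25 SD or less at both times, r is at most 0.02 and the rate stays near 5%.

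**Dependence on the mix.** Let a fraction p of patients be diabetic and D SDs higher at both times. Then r = p(1−p)D² / [p(1−p)D² + 1]. For D = 1.5, p = 0.5 gives 0.5625/1.5625 = 0.36, and p = 0.1 gives 0.2025/1.2025 = 0.17. Nothing about the patients has changed, only the quota.

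**ANS relationships.** Section 3.12 uses the same methods there, and section 3.11 separates the groups by beta-blocker treatment (groups 1, 2 and 4 treated, group 3 not). The same mechanism could operate, but no magnitude was computed.

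**The case against.** The case on the other side has real force.

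- *Pooling is inferred.* Section 3.12 does not say that the coefficients are taken over all 120 patients. Section 3.11 says the groups exist to describe the relationship in diabetic and in non-diabetic patients, and it sizes the study for accuracy in each group. A univariate regression run inside one group complies with section 3.12 and has no between-group component. This stands: the text allows that reading, although the split between primary and secondary objectives makes a pooled primary analysis the more natural one.
- *The primary outcome is something else.* A reader might infer that the trial's primary result is invalid. The documents do not support that. Sections 3.8 and 3.12 define the primary outcome as the mean paired CV difference with its interval, section 3.11 sizes the study on it, and this issue does not touch it.
- *The pooled association is not false.* A reader might call the rates above false-positive rates for the primary objective. They are errors only if the coefficient is read as a within-group relationship. If diabetic patients are higher at both times, the association in the whole sample exists, and the objective is only to describe. This stands, with the reservation that under quota sampling the overall coefficient describes no defined population.
- *A postoperative gap is not documented.* Section 1 supports only a baseline difference, cautiously and without a size. Section 3.5 puts every patient on one insulin protocol with one target, which might narrow gaps after surgery. This also stands, and scenario 1 shows that the effect then disappears.

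Leaving covariates to an unseen analysis plan answers less: the article itself specifies univariate models.

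**Conclusion.** The point holds as a should-fix. On its natural reading, section 3.12 investigates the relationship in the primary objective with a pooled one-predictor analysis over quota groups that the protocol itself expects to differ at baseline. Such a coefficient cannot show that a patient's preoperative variability relates to postoperative variability beyond group membership.

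The size cannot be fixed from the documents. At SD 8.2 with no within-group relationship, it runs from nothing (no postoperative gap) through r of 0.08 and 0.11 to 0.17 in the scenarios worked here. Even 0.17 is only about 3% of variance (0.17² = 0.029). All of this rests on assumed group means and on gaps being present at both times.

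The documents do not support the stronger conclusion that the trial will give a false primary answer: pooling is inferred, the target is not declared to be within-group, and the named primary outcome is unaffected.

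**What to change.** In section 3.12:

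- Regress postoperative CV on baseline CV with the four-level group factor in the model. Report the within-group slope and the partial correlation, each with a 95% CI.
- For the secondary objective by diabetic status and surgery, give group-specific coefficients or a baseline-by-group interaction. This also shows whether a common slope is a fair summary.
- Show the pooled coefficient only beside these, labelled as a description of this quota sample.
- Use the same group factor for the relationships between glucose variability and ANS activity.

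The cost is 3 degrees of freedom (118 to 115 in the residual) and a few lines of text. Group membership is already known for every patient, so no new data are needed and the sample size does not change. If the groups do differ at both times in the same direction, the reported coefficient will probably be smaller than the pooled one.

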### 3.5. Study procedure and patient management

Eligible patients will be screened and informed during the anesthesia consultation. Written informed consent will be obtained the same day by investigators after an oral explanation of the study.

After inclusion in the study, patient characteristics, past medical history including ASA physical status and Euroscore value, and preoperative fasting BG and glycosylated hemoglobin values will be collected.

All patients will be admitted to the Cardiac Surgery Department the day before surgery. All patients included in the study will be managed according to the current practices for the management of patients undergoing planned cardiac surgery. Briefly, on arrival in the operating room, standard monitoring (Carescape B850 monitor, General Electric Healthcare, USA) will be set up. A dedicated peripheral venous catheter will be inserted in a forearm vein to infuse anesthetic drugs. All patients will receive manually driven target^-^controlled infusion of propofol and remifentanil to maintain bispectral index (BIS) values between 40 and 60. All patients will be paralyzed using non depolarizing neuromuscular blocking agent (either cisatracurium or atracurium). After induction of anesthesia, patients will be intubated, and tidal volume and respiratory rate will be set to maintain the end^-^tidal carbon dioxide between 35 and 40 mm Hg. Inspired oxygen fraction will be adjusted to obtain a pulse oximetry ≥ 95%. A central venous catheter inserted in the internal jugular vein, a urinary catheter and an indwelling arterial catheter introduced in a radial artery will be implemented. No intravenous glucose will be administered intraoperatively in the absence of hypoglycemia (defined as <75 mg/dL [4.1 mmol/L]). Tranexamic acid (1.5 g before incision and 1.0 g before surgical wound closure) and antibiotic prophylaxis with cefuroxime (1.50 g before skin incision, reinjection at priming of the extracorporeal circulation and then 0.75 g every 2 h until end of surgery) or linezolid 600 mg in case of allergy to cefuroxime will be initiated before incision.

Intraoperative data describing the surgical procedure and the anesthetic management will be obtained from the computerized anesthesia monitoring sheet: type and duration of surgery; duration of aortic cross clamping; duration of extracorporeal circulation; intraoperative blood loss and urine output; intraoperative blood transfusion and total volume of fluids infused.

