### 3.9. Laboratory measurements

Blood and urinary levels of biomarkers of inflammation (IL-2, IL-6, IL-10, TNF-alpha, 8-iso^-^prostanglandin^-^F_2*α*_) and of endothelial function [Endocan, angiopoietin^-^1 (Ang^-^1), angiopoietin^-^2 (Ang^-^2), vascular endothelial (VE)^-^cadherin] will be measured from blood and urinary samples performed the day before surgery, on arrival in the ICU and at 24 hours and at 48 hours after admission in the ICU. Additional blood and/or urinary analysis will be performed if necessary, depending on the hypotheses formulated from the results of the study.

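### The single-predictor analysis of postoperative BG variability against biomarkers (3.12) cannot separate BG variability from operative duration, diabetes status or type of surgery, although all three are recorded

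*Protocol article*

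**What the plan says.** Section 3.12 assigns three sets of relationships to one method, among them that "between the postoperative BG variability and the blood and urinary level of biomarkers of inflammation and endothelial function". The method is a Pearson or Spearman correlation, together with "univariate linear regression models and presented on adequate figures". In context this means one predictor per model: no covariate, stratification or multivariable model is named for this relationship.

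Section 3.5 collects intraoperative data for every patient, including "duration of aortic cross clamping; duration of extracorporeal circulation". Section 3.12 gives these durations no role in any analysis.

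Under section 3.9 the samples are "performed the day before surgery, on arrival in the ICU and at 24 hours and at 48 hours after admission in the ICU". Three of the four sampling times therefore follow the operation, as does the 48-hour window in which section 2 sets postoperative BG variability.

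Section 3.2 defines four groups of 30: insulin-requiring type 2 diabetes with CABG, non-insulin-requiring type 2 diabetes with CABG, no diabetes with aortic valve replacement, and no diabetes with CABG.

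The objective in section 2 is secondary and descriptive: "to describe the relationship between postoperative BG variability within 48 hours after surgery and the urinary and blood level of biomarkers of inflammation". Endothelial markers are covered as well.

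**The concern.** Exposure and outcome are both measured after the same operation. A longer time on bypass could plausibly raise inflammatory or endothelial markers and also disturb glucose. If so, the two would be correlated even with no link between them. Patient group raises the same problem in a pooled analysis. The cohort deliberately mixes diabetes phenotypes and two operations, and the introduction itself reports that basal BG variability seems to depend on diabetes phenotype. If marker levels also differ by group, part of the pooled correlation is a contrast between groups.

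The other design features do not remove this. The sample taken the day before surgery deals with the preoperative marker level, not with the operation. Group membership does not stand in for bypass duration, which can vary between operations within a group.

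What is at stake is interpretation. The introduction cites work in which "the deleterious effect of BG variability includes increased oxidative stress, endothelial dysfunction, and cell apoptosis", says the mechanisms remain unclear in cardiac surgery, and places the biomarker relationship in the study aim. An unadjusted association could easily be taken as evidence on that mechanism when it reflects the size of the surgical insult or the mix of patients.

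**Working it through.** **The plan's own figure.** The biomarker analysis has no sample size or power statement of its own. The patient numbers come from section 3.11, where the 95% interval of one mean has full width 2 × t(0.975; n−1) × SD / √n. With SD 8.2 and n = 30 this gives 6.124, against 6.12 stated, so the figure of 30 per group (120 in total) reproduces up to rounding. Section 3.12 does not say whether the biomarker relationship is examined in the pooled cohort or within groups, so both 120 and 30 are used below.

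**Inputs.** Let T be extracorporeal circulation duration, V postoperative BG variability and B a postoperative biomarker. The documents give no correlation among these. *Assumption:* corr(T,V) = corr(T,B) = a, with a from 0.2 to 0.5, no direct V–B link, and a two-sided 5% test.

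**Formulas.**
- Induced correlation: r(V,B) = a × a = a².
- Partial correlation given T: [r(V,B) − r(T,V) r(T,B)] / √{[1 − r(T,V)²][1 − r(T,B)²]}. This is zero when r(V,B) = a².
- The critical |r| is 0.179 at n = 120 and 0.361 at n = 30.

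**Unadjusted rejection rates** (simulation, 20,000 runs per setting):

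| a (assumed) | induced r | n = 120 | n = 30 |
|---|---|---|---|
| 0.2 | 0.04 | 7% | 6% |
| 0.3 | 0.09 | 16% | 8% |
| 0.4 | 0.16 | 41% | 13% |
| 0.5 | 0.25 | 79% | 27% |

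*Check by Fisher z at a = 0.4, n = 120:* atanh(0.16) = 0.1614; times √117 = 10.82 gives 1.746; 1.960 − 1.746 = 0.214; the upper-tail probability is about 0.415, which agrees with 41%.

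With T in the model the simulated rate is about 5% in every row. That holds only because T is the sole common cause in the simulation.

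**Group.** The documents give no marker levels by group, so the group component cannot be given a figure. It works in the same way in a pooled analysis, and a model with duration alone would leave it in place.

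**Cost of adjusting.** The covariates are one term for duration and three group indicators, so four degrees of freedom. Residual degrees of freedom fall from 120 − 2 = 118 to 120 − 6 = 114. For duration alone, the standard error of the BG variability coefficient grows by 1/√(1 − a²), which is 1.02 at a = 0.2 and 1.15 at a = 0.5, before any gain from smaller residual variance. Group adds to this by an amount that cannot be computed from the documents.

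**The case against.** The strongest reply is that the objective is to describe a relationship, and an unadjusted correlation is a valid answer to a descriptive question. This stands in part. A reader might infer from the mechanistic introduction that the association will be reported as BG variability driving inflammation. The documents do not support that: no section plans a causal statement, and the harmful effect of variability appears only as background from other studies. Misreading is a risk, not a stated intention. The reply is still incomplete, because the study aim follows directly on a passage about unclear mechanisms.

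Second, no section shows that a longer operation raises either variable. The constant glucose infusion and hourly insulin protocol (3.5) may weaken the path to glucose, and the exclusion of combined and emergent surgery (3.4) may narrow the spread of durations. This stands. It is why the range starts at 0.2, where the error rate hardly moves.

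Third, adjusting for bypass duration does not by itself restore a 5% error rate in this cohort, because diabetes status and type of surgery remain. This also stands, and it is why group belongs in the model. Nor do the documents show how closely cross-clamp time follows bypass time, so using one duration is a matter of economy and makes no claim about their correlation.

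Finally, the durations are collected, so adjustment remains possible at analysis. That is true, but an adjustment chosen after seeing the data is weaker evidence than a prespecified one.

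**Conclusion.** The point holds as a limitation of a stated method. Section 3.12 fixes a single-predictor analysis for the biomarker relationship, so the protocol is not merely silent here. That analysis cannot distinguish an association with BG variability from one produced by operative duration, diabetes status or type of surgery.

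The size is unknown and could be negligible or large: about 7% to 79% false-positive results at n = 120, and 6% to 27% at n = 30. These figures rest on assumed equal correlations of 0.2 to 0.5 between bypass duration and both variables, and on no direct link. They do not show that confounding is present.

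The point concerns a secondary objective. The primary outcome, the mean within-patient difference in the coefficient of variation with its confidence interval (3.8), is unaffected. The change is worth making because it is cheap and uses data already recorded; the study does not depend on it.

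**What to change.** In section 3.12:

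- Add a prespecified linear model of each postoperative biomarker on postoperative BG variability, with extracorporeal circulation duration and patient group (four levels) as covariates.
- Report the adjusted BG variability coefficient, with its confidence interval, next to the unadjusted one.
- State that the unadjusted association is descriptive and not to be read causally.

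The adjusted estimate still allows only for the named covariates, and the report should say so.

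The cost is a few sentences in 3.12, four degrees of freedom among 120 patients and a somewhat wider interval. No new data are needed. The correlations and figures already planned remain, so the descriptive objective is kept.
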